**Not applicable**

Study procedures will be conducted at UVM Buprenorphine Research Clinic, which has been the site of BUP research for the past 25 years. The clinic is located in our University Medical Center's outpatient building and is contiguous with our other research clinics for cocaine dependence and smoking cessation as well as our methadone clinic for which [name] is Director. IBT participants will visit the clinic every 2 weeks while receiving the IBT package described above. WLC participants will remain on the waitlist for their treatment of choice, though they will complete the same scheduled follow-up assessments as IBT participants. WLC participants who have not entered treatment by Week 24 will be offered the opportunity to cross over to IBT at that time, contributing additional within-subject data with which to evaluate the efficacy of the IBT intervention. The intake assessment will include a Drug History Questionnaire, ASI (McLellan et al., 1985), psychoactive substance dependence section of the DSM-5 (APA, 2013), Brief Symptom Inventory (Derogatis, 1993), Beck Depression and Anxiety Inventories (Beck et al., 1988, 1996), Michigan Alcoholism Screening Test (Selzer, 1971) and a Time-Line Followback of past-month use of opioids and other drugs (Sobell & Sobell, 1992). Participants will also complete a medical history, receive a brief physical exam, and provide a urine specimen (see *Biochemical monitoring*). Follow-up assessments will consist of abbreviated versions of the intake, will include urinalysis, and be administered monthly during the 6-month trial (i.e., at Weeks 4, 8, 12, 16, 20, and 24).

**Statistical Considerations:** Delineate the precise outcomes to be measured and analyzed. Describe how these results will be measured and statistically analyzed. Delineate methods used to estimate the required number of subjects. Describe power calculations if the study involves comparisons. Perform this analysis on each of the primary and secondary objectives, if possible.

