**Statistical methods.** IBT and WLC groups will be compared on baseline characteristics using analyses of variance for continuous and chi-square tests for categorical variables. If characteristics differ significantly and are predictive of outcome, they will be considered as covariates in subsequent analyses. The primary outcome will be the percent of participants in IBT and WLC conditions with biochemically-confirmed illicit opioid abstinence at the 24-week assessment, evaluated based on a chi square test. Primary analyses will include all randomized subjects independent of early dropout and with missing urine specimens considered positive for illicit opioids, consistent with an intent-to-treat approach (Armitage, 1983). We hypothesize that participants receiving IBT will achieve significantly greater biochemically-verified illicit opioid abstinence relative to WLC. If applicable, logistic regression will be used to adjust for baseline covariates confounded with treatment group. Though not the primary outcome, abstinence at the other monthly assessments will be compared between groups with Bonferroni-adjusted chi square tests to control experiment-wise type I error rate below  $\alpha=.05$ . Within the IBT group, generalized estimating equation (SAS, PROC GENMOD) will be used to characterize the temporal trend in abstinence across monthly assessments. Additional outcomes will include IV opioid use, other (non-opioid) drug use, retention, BUP adherence, IVR utilization, and patient satisfaction. Repeated measures analyses of variance (SAS, PROC MIXED) will be used to compare groups on continuous outcomes (e.g., past-month frequency of illicit opioid and IV use, ASI subscales, BDI, HIV+HCV knowledge). If significant treatment by time interactions are detected, partial F-tests will be used to examine simple effects of treatment at each assessment. Additional repeated measures analyses will characterize temporal patterns in IBT-specific outcomes (e.g., BUP adherence, IVR utilization, satisfaction). Statistical analyses will be performed using SAS statistical software Version 9.4.

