**SUBJECT CHARACTERISTICS, IDENTIFICATION AND RECRUITMENT**

**Subject Selection:** Provide rationale for subject selection in terms of the scientific objectives and proposed study design.

Subjects will be adults with current opioid use disorder who are waitlisted for methadone or buprenorphine treatment

**Vulnerable Populations:** Explain the rationale for involvement of special classes of subjects, if any. Discuss what procedures or practices will be used in the protocol to minimize their susceptibility to undue influences and unnecessary risk (physical, psychological, etc.).

☒ **Not applicable**

**Number of Subjects:** What is the anticipated number of subjects to be enrolled at UVM/UVM Medical Center and in the case of a multi-center study, with UVM/UVM Medical Center as the lead, the total number of subjects for the entire study.

The anticipated number of subjects to be enrolled in the study is 100 (50 per experimental condition).

**Inclusion/Exclusion Criteria:** Eligibility and ineligibility criteria should be specific. Describe how eligibility will be determined and by whom. Changes to the eligibility criteria at a later phase of the research have the potential to invalidate the research.

Participants must be  $\geq 18$  years old, in good health, meet DSM-5 criteria for opioid use disorder and provide an opioid-positive urine at study intake. Consistent with our prior BUP studies, those with a significant psychiatric or medical illness that may interfere with consent or participation will be excluded, as will those who are pregnant or nursing. Those dependent on sedative-hypnotics will be excluded, due to the medical risks and notably low success rates with sedative-dependent opioid abusers (Stitzer & Chutuape, 1999). Intake information will be reviewed by the PI ([name]) and study physician ([name]), who will determine and document whether the participant is eligible and healthy to participate.

**Inclusion of Minorities and Women:** Describe efforts to include minorities and women. If either minorities or women are excluded, include a justification for the exclusion.

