### Summary of important changes after Trial 1 commencement:

- 1.) Given changes in treatment availability in Vermont between the pilot and present studies, the inclusion criterion that participants be waitlisted for agonist maintenance was modified to include participants not currently receiving opioid agonist treatment.
- 2.) The target sample size was changed to 50 in concert with similar changes requested by funding agency for the parallel Trial 2.
- 3.) The Brief Pain Inventory (Cleeland, 1989, 1990; Keller et al., 2004) was added to the assessment battery.
- 4.) The opioid overdose educational module (below) was added to the intervention.
- 5.) HIV, HCV, and opioid overdose knowledge post-tests were added to the Week 4 assessment.
- 6.) Compensation for intake and monthly assessments was increased from \$30 to \$75 to facilitate timely recruitment.
- 7.) With the onset of the COVID-19 pandemic, the following modifications were made to the study protocol in situations where participants were at high-risk and/or currently experiencing COVID-19 symptoms: participants were permitted meet with study staff less frequently or remotely via phone or UVM's institutionally-supported Zoom platform to reduce the risk of COVID-19 transmission; biochemical samples may be omitted or collected using modified procedures to reduce risk of COVID transmission.

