### Statistical methods

IBT and WLC groups will be compared on baseline characteristics using analyses of variance for continuous and chi-square tests for categorical variables. If characteristics differ significantly and are predictive of outcome, they will be considered as covariates in subsequent analyses. The primary outcome

will be the percent of participants in IBT and WLC conditions with biochemically-confirmed illicit opioid abstinence at the 24-week assessment, evaluated based on a Cochran-Mantel-Haenszel (C-M-H) chi square test with site as the stratification variable. Primary analyses will include all randomized subjects independent of early dropout and with missing urine specimens considered positive for illicit opioids, consistent with an intent-to-treat approach (Armitage, 1983). The Breslow-Day test will be used to test homogeneity of the treatment effects across sites. If applicable, logistic regression will be used to adjust for baseline covariates confounded with treatment group. Though not the primary outcome, abstinence at other monthly assessments will be compared across treatments with Bonferroni-adjusted C-M-H tests to control experiment-wise type I error rate below  $\alpha=.05$ . Within the IBT group, generalized estimating equation (SAS, PROC GENMOD) will be used to characterize the temporal trend in abstinence across assessments. Fixed factors will include recruitment site and the within-subject factor, assessment time, along with their interactions. Repeated measures analyses of variance (SAS, PROC MIXED) will be used to compare groups on continuous outcomes (e.g., past-month frequency of illicit opioid and IV use, ASI subscales, BDI, HIV knowledge, OD risk knowledge). If significant treatment by time interactions are detected, partial F-tests will be used to examine simple effects of treatment at each assessment. Additional repeated measures analyses will characterize temporal patterns in IBT-specific outcomes (e.g., BUP adherence, IVR utilization, satisfaction). For WLC participants who after 24 weeks transition to IBT, estimates of abstinence will be obtained with corresponding 95% confidence intervals at each assessment. Statistical analyses will be performed using SAS V9.4 (SAS Institute, Cary, NC).

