### Summary of important changes after trial commencement (Trial 2):

- 1.) Given changes in treatment availability in Vermont between the pilot and present studies, the inclusion criterion that participants be waitlisted for agonist maintenance was modified to include participants not currently receiving opioid agonist treatment.
- 2.) Following an initial request (prior to trial commencement) by the funding agency to increase the originally-proposed 12-week duration to a similar 24-week duration in order to parallel that of Trial 1, the proposed sample size was then also reduced to align with that of parallel Trial 1.
- 3.) HIV, HCV, and opioid overdose knowledge post-tests were added to the Week 4 assessment.
- 4.) Compensation for intake and monthly assessments was increased from \$30 to \$75 to facilitate timely recruitment.
- 5.) Remote study sites were broadened to include locations that were convenient to participants (e.g., municipal office, fire station, community substance treatment facility).
- 6.) With the onset of the COVID-19 pandemic, the following modifications were made to the study protocol in situations where participants were at high-risk and/or currently experiencing COVID-19 symptoms: participants were permitted meet with study staff less frequently or remotely via phone or UVM's institutionally-supported Zoom platform to reduce the risk of COVID-19 transmission; biochemical samples may be omitted or collected using modified procedures to reduce risk of COVID transmission.

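### With about 25 IBT participants per trial, a GEE that tests the six visits as a factor is unreliable; prespecify one linear trend with small-sample-valid inference

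*Supplement*

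**What the plan says.** **Trial 1, Statistical methods.** Within the IBT arm, "generalized estimating equation (SAS, PROC GENMOD) will be used to characterize the temporal trend in abstinence across monthly assessments". The assessments are monthly ("i.e., at Weeks 4, 8, 12, 16, 20, and 24"). The text does not say whether time is categorical or linear. It also names no test (Wald or score), working correlation or small-sample adjustment, and attaches no significance level to this analysis.

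**Trial 2, Statistical methods.** The same kind of GEE is planned, but the model is spelled out further: "Fixed factors will include recruitment site and the within-subject factor, assessment time, along with their interactions".

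**Sample size.** Trial 1, Number of Subjects, gives the size for which the method was written: "The anticipated number of subjects to be enrolled in the study is 100 (50 per experimental condition"). Trial 2 was written for 200, with 100 per arm. The change lists then reduce both. For Trial 1, "The target sample size was changed to 50 in concert with similar changes requested by funding agency for the parallel Trial 2"; for Trial 2, "the proposed sample size was then also reduced to align with that of parallel Trial 1". Neither list revises the GEE.

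**The concern.** The GEE's robust (sandwich) variance is a large-sample device, and what counts is the number of people, not the number of urine specimens. With about 25 people, a joint test on several degrees of freedom leans heavily on a poorly estimated covariance matrix. The direction of the error depends on the test: Wald rejects too often and score too rarely.

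This bears on something the trials want to know. The stated objective is whether the IBT effect lasts, and the sample size section expects abstinence to fall as treatment lengthens to 24 weeks. The pilot already showed 88%, 84% and 68% at Weeks 4, 8 and 12. The primary test compares the arms at a single visit, so the GEE is the only planned model of the course of abstinence within IBT. A test that misses a real decline about half the time, or flags change where there is none, describes that course badly.

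**Working it through.** **The plan's own figures.** For 50 per arm and 60% vs 15%, a two-proportion calculation gives 99.9% power, in line with the stated figure of more than 95%. A 30-point difference at its least favourable position (65% vs 35%) gives 86.2%, and ES 0.56 gives 80.0%, again as stated. The documents give no error rate or power for the GEE, so there is none to reproduce.

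**Inputs.**
- Visits: 6, hence 6 - 1 = 5 df if time is a factor, and 1 df if linear.
- People: 50 / 2 = 25 in IBT (assumes 1:1 is kept).
- Significance level: 0.05 two-sided (assumed here; the plan uses it for power and to "control experiment-wise type I error rate below" that level for the between-group tests).
- Within-person correlation: not in the documents; varied from 0.2 to 0.8.
- Abstinence under no trend: 50-80%, which covers the planning value of 60%.
- Data complete at every visit, as follows if missing specimens count as positive here too.

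**Why the two 5-df tests err in opposite directions.** Let d be the five differences between later visits and the first, and A the estimated covariance of those contrasts about the visit means. On the scale of proportions:
- Wald: W = n d'A⁻¹d.
- Score: the covariance is taken about the overall mean, so A becomes A + dd', and S = W / (1 + W/n).
- Both are referred to chi-square(5), critical value 11.07.
- At n = 25 the score test therefore rejects only if W > 11.07 / (1 - 11.07/25) = 11.07 / 0.5572 = 19.87. At n = 50 the bar is 11.07 / (1 - 11.07/50) = 14.22.
- The Hotelling-type F(5, 20) critical value on the W scale is 16.94 at n = 25. The Wald cut-off of 11.07 is below it and the score test's 19.87 above it.

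**Simulation on the logit scale, n = 25, six visits.** Data were exchangeable, autoregressive or random-intercept.

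| Test | False positives, flat rate | Power, 88% falling to 55% |
|---|---|---|
| 5-df Wald | about 9-12% | not compared, size not held |
| 5-df score | about 0.2-3% at moderate to high correlation; 2.6-4.8% at 0.2 | about 38-53% |
| 1-df linear, uncorrected Wald | about 6-7% | about 92-99% |
| 1-df linear, score | about 4-5% | about 92-99% |
| 1-df linear, Mancl-DeRouen | about 5-6% | about 92-99% |

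- Edges of the grid: at 80% abstinence the 5-df Wald rate is 10.0-13.5%. At correlation 0.8 it is 4-9% for abstinence of 50-68%, but the covariance matrix is then often singular.
- Changing only the reference distribution is not enough. Referring the logit Wald statistic to F(5, 20) gives 0.8-2.5%, which is conservative.
- At n = 50, correlation 0.2-0.6: 5-df Wald 6.2-8.2%, 5-df score 2.4-4.7%, and score-test power for the same decline 97-99%.
- For a milder decline, 80% to 60%, at n = 25: 5-df score 8-17%, corrected 1-df trend 55-73%.

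**Trial 2 with site-by-time.** The planned recruitment shares were one half at the university and one quarter at each rural clinic. Applied to 25 people, that is about 13, 6 and 6, so 3 x 6 = 18 site-visit cells.
- At 60% abstinence a cell of 6 is all negative or all positive with probability 0.6⁶ + 0.4⁶ = 0.047 + 0.004 = 0.051.
- The two small sites have 12 such cells, so 12 x 0.051 = 0.61 are expected per trial. Any one of them makes a logit infinite.
- In simulation only 57-65% of datasets had no such cell and full rank. Among those, the Wald test of time rejected in 13.2-15.2%.
- With two site groups of 13 and 12, the Wald rate was 11.1-12.7%.

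**The case against.** The strongest reply is that Trial 1 contains no 5-df test. It speaks only of a temporal trend, and a linear trend is at least as natural a reading. Under it, PROC GENMOD's uncorrected score test already holds its size and has high power, so neither a new SAS procedure nor a corrected variance is needed to make the test valid. This stands. The power gain also comes from using 1 df against a steady decline, not from the variance correction.

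Other parts also stand:
- The correlation and the 25 per arm are assumptions.
- The 5-df Wald test was already somewhat liberal at 50 per arm, so the reduction aggravates that fault rather than creating it. What the reduction does change sharply is the score test's power.
- The analysis is secondary and single-arm, with no stated significance level.

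Two stronger readings are tempting. A reader might infer that the planned GEE has wrong error rates in both trials whatever its coding. The documents do not support that, because Trial 1 leaves the coding open and one ordinary choice works. A reader might also infer that a non-significant trend would be reported as proof of a lasting effect, but no passage ties such a claim to this test.

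The reply does not dispose of Trial 2, where time is called a factor and is crossed with site. In Trial 1 the open choice itself matters: the candidate tests differ in false-positive rate from below 1% to about 12%.

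**Conclusion.** The point holds in a conditional form. With about 25 IBT participants per trial, the within-IBT GEE is unreliable if visits are tested as a six-level factor. Trial 2 states that coding and Trial 1 permits it. False positives are then about 9-12% for Wald and about 0.2-3% for score at moderate to high correlation (up to about 5% at correlation 0.2). Score-test power for a fall from 88% to 55% drops from 97-99% at 50 people to about 38-53% at 25. With Trial 2's site-by-time terms the Wald rate is about 11-15% and the model often cannot be fitted. A 1-df linear trend avoids most of this.

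These sizes rest on an assumed within-person correlation, 1:1 allocation of 50, the 5% level, complete data and, for Trial 2, recruitment in the original site proportions. The primary Week 24 comparison is not touched. The change is worth making because it is cheap and concerns the only model of abstinence over time within IBT.

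**What to change.** In Statistical methods of both protocols:

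1. Prespecify one 1-df linear trend in abstinence over Weeks 4-24 within IBT.
2. Test it with the PROC GENMOD score test, or with a small-sample-corrected sandwich variance such as Mancl-DeRouen. Use the corrected variance for the slope's standard error and confidence interval in either case.
3. In Trial 2, drop the site-by-time terms. Site may stay as a main effect, though that model was not simulated here.
4. Report abstinence at each visit with an exact or Wilson 95% confidence interval.

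The cost is a few sentences and, for the corrected variance, a different SAS option or procedure. A linear trend is less sensitive to a course that falls and then recovers, but the per-visit proportions would show it. Trial 2 gives up a formal look at whether the trend differs by site, which about 6 people at each small site could not have supported.

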**Sample size justification.** The proposed sample size is based on having sufficient power for detecting treatment differences for both primary and secondary outcomes. Regarding the primary outcome measure, the percent of participants negative for illicit opioids at the 24-week assessment, power is estimated to be greater than 95% using  $\alpha=.05$  if true abstinence rates are as low as 60% vs. 15% for IBT and WLC groups, respectively. These estimates are more conservative than our R34 outcomes, with lower abstinence predicted in IBT as we increase the duration to 24 weeks. Furthermore, power is estimated to be 80% or more to detect group differences as low as 30% in 24-week abstinence rates ( $ES=0.56$ ). For secondary outcomes, effect sizes range from small to moderate. The estimated mean

differences and minimum detectable effect sizes corresponding to 80% power ( $\alpha=.05$ ) for detecting treatment group differences in the change from baseline to Week 24 for representative ASI subscales are: Employment=.118 (ES=0.32), Psych=.107 (ES=0.51), Legal=.062 (ES=0.45), and Drug=.079 (ES=0.72). Similarly, power is 80% for detecting a mean difference of 5.5 units in the 24-week change in BDI (ES=0.42), which is smaller than we observed in our pilot trial. Lastly, power is estimated to be 80% to detect a mean absolute difference of 8.5% in the pre-post change in HIV knowledge scores (ES=0.54). It should be noted that these effect sizes (Cohen d's) are expressed relative to the between-subject variability at baseline [i.e.  $(\Delta_{IBT}-\Delta_{WLC})/\sigma_{\text{between-subject}}$ ], not the variability in the change scores [i.e.  $(\Delta_{IBT}-\Delta_{WLC})/\sigma_{\Delta}$ ] (Becker, 1988; Morris, 2008). The actual computation accounts for the correlation observed across repeated assessments for each outcome observed in our pilot data which is responsible for the different estimates of detectable ES's.

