### **Sample size justification**

The proposed sample size is based on having sufficient power for detecting treatment differences for primary and secondary outcomes. Regarding the percent of participants negative for illicit opioids at the 24-week assessment, power is estimated to be greater than 95% using  $\alpha=.05$  if true abstinence rates are as low as 60% vs. 15% for IBT and WLC groups, respectively. These estimates are more conservative than on our R34 outcomes, with lower abstinence predicted in IBT as we increase the duration to 24 weeks and move beyond a single research clinic for this Stage II trial. For secondary aims, effect sizes range from small to moderate. The estimated differences between conditions in mean change from baseline to 24 weeks corresponding to power=80% for representative ASI subscales are: Employment=.084 (ES=0.23), Psych=.076 (ES=0.36), Legal=.044 (ES=0.32), and Drug=.056 (ES=0.51). Similarly, power is 80% for detecting a mean difference of 4 units in the 24-week change in BDI (ES=0.30) which is smaller than we observed in our pilot trial. Lastly, power is estimated to be 80% to detect a mean absolute difference of 6% in the pre-post change in HIV knowledge scores (ES=0.39) and 5.5% (ES=0.34) for the pre-post change in OD knowledge scores. It should be noted that these ES's (Cohen d's) are expressed relative to the between-subject variability at baseline [i.e.  $(\Delta_{IBT}-\Delta_{WLC})/\sigma_{\text{between-subject}}$ ], not the variability in the change scores [i.e.  $(\Delta_{IBT}-\Delta_{WLC})/\sigma_{\Delta}$ ] (Becker, 1988; Morris, 2008). The actual computation accounts for the correlation observed across assessments for each outcome observed in our pilot data which is responsible for the different estimates of detectable ES's.

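### Continuous secondary outcomes: no baseline-score adjustment is pre-specified, and covariates enter only through baseline significance and outcome prediction, so precision is lost and chance imbalance can shape the model

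*Supplement*

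**What the plan says.** The two protocols in the Supplement treat continuous outcomes in the same way.

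- **Analysis (Statistical methods, Trials 1 and 2).** "Repeated measures analyses of variance (SAS, PROC MIXED) will be used to compare groups on continuous outcomes". A significant treatment-by-time interaction leads to tests of the treatment effect at each assessment. The text does not say whether baseline is a level of the time factor, and it does not list the outcome's baseline score as a covariate.
- **Covariates (same sections).** "If characteristics differ significantly and are predictive of outcome, they will be considered as covariates in subsequent analyses". Both conditions must be met.
- **Power (Sample size justification).** The contrast is change from baseline. Trial 1 gives 80%-power figures "for detecting treatment group differences in the change from baseline to Week 24 for representative ASI subscales", namely "Employment=.118 (ES=0.32), Psych=.107 (ES=0.51), Legal=.062 (ES=0.45), and Drug=.079 (ES=0.72"). It adds a "mean difference of 5.5 units in the 24-week change in BDI (ES=0.42") and a "mean absolute difference of 8.5% in the pre-post change in HIV knowledge scores (ES=0.54"). Trial 2 does the same: "The estimated differences between conditions in mean change from baseline to 24 weeks corresponding to power=80% for representative ASI subscales". Effect sizes are scaled by the baseline between-subject SD. The calculation uses pilot correlations whose values are not reported.
- **Baseline data.** ASI, BDI and Time-Line Followback are in the intake battery for all participants (Assessments, both trials). The knowledge pre-tests are described only as a Week 1 component of IBT (HIV+Hepatitis education, both trials; Overdose prevention, Trial 2).

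**The concern.** In a randomized comparison a continuous outcome can be compared as a raw follow-up mean, as change from baseline, or adjusted for baseline. The first two fix the weight on the baseline score at 0 or 1. Adjustment estimates that weight, so apart from one degree of freedom it is never less precise in expectation than either. The plan powers on change, tests raw visit means as simple effects, and leaves adjustment to a data-driven rule.

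Under randomization, a significance test at baseline is a poor trigger. A strongly prognostic baseline score deserves adjustment whatever its p-value, and the rule lets chance imbalance help choose the final model. The requirement that the covariate predict outcome adds a second data-dependent step.

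Precision matters here because the sample size was justified for secondary as well as primary outcomes, and the target was later reduced.

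**Working it through.** **Inputs.** From the two Sample size justification sections: alpha 0.05 (taken as two-sided), 80% power, 50 per arm (Trial 1) and 100 per arm (Trial 2), and the stated effect sizes (ES) in baseline SDs. Assumption for the main results: equal SDs at baseline and Week 24.

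**1. Reproduce the base figure.** The standardized difference with 80% power at 50 per arm is d = (1.96 + 0.84) × √(2/50) = 0.56, matching the 0.56 given in Trial 1. The noncentral t gives 0.566, used below. At 100 per arm it gives 0.398.

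**2. Back-solve the correlation rho.** With equal SDs the SD of change is σ√(2(1−rho)), so ES = d√(2(1−rho)) and rho = 1 − (ES/d)²/2. For ASI Drug: (0.72/0.566)² = 1.62 and rho = 1 − 0.81 = 0.19.

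**3. Compare variances.** Change: 2(1−rho)σ². Baseline-adjusted: (1−rho²)σ². Ratio: (1+rho)/2. Raw Week 24 means: σ², so the saving against them is rho².

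**4. Power after adjustment** at the stated differences: Φ(2.80/√ratio − 1.96).

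| Outcome | ES, Trial 1 | rho, Trial 1 | rho, Trial 2 | Ratio to change | Power (80% by change) | Saving vs raw Week 24 mean |
|---|---|---|---|---|---|---|
| ASI Employment | 0.32 | .84 | .83 | .92 | 83% | 70% |
| BDI | 0.42 | .73 | .72 | .86 | 86% | 52% |
| ASI Legal | 0.45 | .68 | .68 | .84 | 86% | 47% |
| ASI Psych | 0.51 | .59 | .59 | .80 | 88% | 35% |
| HIV knowledge* | 0.54 | .55 | .52 | .77 | 89% | 30% |
| ASI Drug | 0.72 | .19 | .18 | .60 | 95% | 4% |

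*Only if a baseline test exists in both arms.

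The Trial 2 correlations use its own ES values (0.23, 0.30, 0.32, 0.36, 0.39, 0.51) and agree closely with Trial 1. For ASI Drug the change score (1.62σ²) is noisier than the raw Week 24 mean (σ²).

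**5. Drop the equal-SD assumption.** Let r be the ratio of the Week 24 SD to the baseline SD, and v = (ES/d)². Then rho = (1 + r² − v)/(2r), and the saving against change is (1 − rho·r)²/v, which cannot be negative. Taking r = 0.8 to 1.2 as an assumed range:

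- Employment (v = 0.32): r = 0.8 gives rho = .825 and (1 − .660)²/0.32 = 36%; r = 1.2 gives rho = .883 and (1 − 1.060)²/0.32 = 1%.
- Drug (v = 1.62): r = 0.8 gives rho = .01 and a saving of about 60%; r = 1.2 gives rho = .34 and about 21%.

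**6. Cost of the covariate.** The variance inflation is about 1 + 1/(N−4): 1.0% at N = 100 and 2.2% at N = 50. With equal SDs the net saving against change at N = 50 is 1 − .92 × 1.022 = 6% for Employment and 1 − .595 × 1.022 = 39% for Drug.

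**7. Reduced target.** If the revised 50 is a total (25 per arm, an assumption), power at the Trial 1 stated differences is Φ(2.80/√2 − 1.96) = 51% by change. With adjustment it is 54% (Employment) to 73% (Drug).

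**The case against.** The best counter-argument is that the analysis text never says outcomes are compared as change. Change appears only in the power sections, and the planned follow-up tests compare group means at each visit. This stands. A reader might infer that the trials analyse change scores, but the documents support that only for the interaction, and only if baseline is a level of time. Against the simple effect at Week 24 the ranking reverses: Drug gains least and Employment most. Some precision is still lost on either reading.

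If baseline is a level of time, PROC MIXED already uses those scores. That alone does not recover the loss. In a seven-timepoint check under compound symmetry, with baseline means left free by arm, the Week 24 simple effect kept the raw-mean variance. Constraining the baseline means to be equal cut the variance of the change contrast by the same fractions as adjustment.

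Other limits also stand:

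- The correlations are derived, not stated, and the size of the saving moves with the SD ratio.
- Adjustment is not literally free. At an SD ratio of 1.2, Employment's saving of about 1% is roughly cancelled by the lost degree of freedom.
- A reader might infer that every baseline value is already collected. For the knowledge scores no waitlist baseline is documented.
- Trial 1's change summary says only that the target became 50, so 25 per arm is a reading, not a stated figure.
- Repeated-measures ANOVA is a valid analysis of randomized groups. No bias in it has been shown.

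**Conclusion.** The point holds as a matter of efficiency and pre-specification for the continuous secondary outcomes of both trials. With back-solved correlations and equal SDs, adjustment saves about 8% to 40% of the variance of the powered change contrast, or about 4% to 70% against an unadjusted Week 24 comparison. With SD ratios of 0.8 to 1.2 the saving against change runs from about 36% to 1% for Employment and 60% to 21% for Drug. The direction does not depend on that assumption; the cost is about 1% of variance at N = 100 and 2% at N = 50. The covariate rule is a separate weakness that does not rest on these figures.

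The documents do not support reading this as invalid inference, or as a defect in the primary chi-square (Trial 1) or Cochran-Mantel-Haenszel (Trial 2) test. The change should be made, but the primary conclusion does not depend on it.

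**What to change.** In Statistical methods for both trials:

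1. Fit post-baseline visits in PROC MIXED with arm, visit, arm × visit, the outcome's baseline score and baseline × visit, plus site in Trial 2. A longitudinal model with a common baseline mean for the two arms is an equivalent choice.
2. Name the adjusted Week 24 difference between arms as the contrast of interest.
3. Delete the rule that admits covariates on baseline significance and prediction of outcome. List fixed covariates in advance.
4. Apply this to ASI, BDI and Time-Line Followback frequencies. Apply it to HIV, HCV and overdose knowledge only if a baseline test is obtained in both arms; otherwise state how those scores will be compared.
5. Report the pilot correlations and SDs behind the power figures, so that the gain can be checked.

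For the intake measures the cost is analysis wording and one degree of freedom. For the knowledge scores it would also mean a baseline test in the waitlist arm.
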